#### Statistics

Data will be collected in a standardized form and transmitted to the Data Monitoring Committee whenever the patient is discharged from the hospital. The completeness and the quality of the data will be checked by a data collector from the Data Monitoring Committee. Logical checks will be performed for missing data and to find inconsistencies. When necessary, the data collector will contact the investigator by phone to validate the data or reformat the data before entry into the database.

The SPSS 21.0 software package will be used for statistical analysis. The counting data will be expressed as the number of patients (percentage) and be analyzed using the chi-square (*χ*^2^) test or Fisher exact test. The normally distributed quantitative variables will be expressed as the mean ± standard deviation (SD). Two independent sample *t*-tests will be used for comparison between groups, and analysis of variance (ANOVA) will be used for comparison at different time points within the groups. Quantitative variables of the skewness distribution will be expressed as the median (interquartile range [IQR]) or mean (95% confidence interval [CI]), and the Mann-Whitney *U* test will be used for comparison. *P* < 0.05 will indicate that the difference is statistically significant. Intention-to-treat will be considered for the patients with an incomplete follow-up period. Missing values will be handled by the mixed model for repeated measurements.

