### Selection and withdrawal of patients

#### Recruitment

Patients admitted to the Neurosurgery Department of the Second Affiliated Hospital of Soochow University for supine surgery under general anesthesia will be screened and recruited during a routine preoperative evaluation. The basic patient information is shown in Table 1. Participants who meet the inclusion criteria will be required to sign an informed consent. The designated staff who performs the preoperative visit will be responsible for obtaining the informed consent.

**Table 1 Tab1:** Baseline patient characteristics

Variables	P6 group	Pi group	*P* value
Gender (male/female)			
Age (years)			
Height (cm)			
Weight (kg)			
BMI (kg/m^2^)			
ASA classification (I–II)			
Smoking (cases): never/ever/within 1 month before surgery			

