#### Randomization

All participants who meet the inclusion criteria will be randomly divided into two groups, P6 group (PEEP = 6 cmH_2_O) or Pi group (individualized PEEP) in a ratio of 1:1. Randomization will be achieved using a computer-generated randomization table. The designated staff will perform the allocation sequence and assign participants to the interventions. This research staff will implement the distribution sequence through sealed and opaque envelopes. Participants will not open the corresponding envelopes until they have completed the experiment. The patients, surgeons, and staff involved in data collection and follow-up visits will be blinded to the grouping; however, the anesthesiologist responsible for the implementation of anesthesia will be aware of the grouping.

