#### Primary and secondary outcomes

The primary outcome of this study is the incidence of pulmonary complications within 1 week following surgery. According to the method adopted by Costa-Leme et al. [25], the modified PPC scoring table will be used as the standard to evaluate the incidence of PPCs after surgery. When a patient has any of the symptoms or signs in Table 2 (e.g., cough, atelectasis, dyspnea, bronchospasm, hypoxemia, hypercapnia, pleural effusion, pneumonia, pneumothorax, mechanical ventilation, endotracheal intubation, respiratory failure) or the score ≥ 1, it indicates that the patient has postoperative pulmonary complications: incidence of pulmonary complications (%) = number of cases with pulmonary complications/total number of patients in this group.

**Table 2 Tab2:** Modified scoring standard of PPCs

Postoperative pulmonary complication score	
**Grade 1**	- Dry cough.
	- Micro-atelectasis: abnormal pulmonary symptoms or signs, body temperature excluding extrapulmonary causes > 37.5 °C; radiologic examination is normal.
	- Dyspnea, excluding extrapulmonary causes.
**Grade 2**	- Cough, expectoration, excluding extrapulmonary causes.
	-Bronchospasm: wheeze or the original wheeze requires changes in treatment.
	- Hypoxemia: SpO_2_ ≤ 90% when breathing air.
	- Atelectasis: radiologic evidence, with a body temperature > 37.5 °C or abnormal lung symptoms or signs.
	- Hypercapnia requiring treatment (PaCO_2_ > 50 mmHg).
**Grade 3**	- Pleural effusion requiring pleural puncture for drainage.
	- Pneumonia: radiologic evidence, accompanied by clinical symptoms (two of the following symptoms: leukocytosis or leukopenia, abnormal body temperature and purulent secretion, and pathologic evidence (Gram staining or bacterial culture) or the use of antibiotics need to be changed).
	- Pneumothorax.
	- Patients need non-invasive mechanical ventilation in all of the following situations: (a) blood oxygen saturation (SpO_2_) is < 92% during oxygen inhalation; (b) during oxygen inhalation, the oxygen flow needs to be > 5 L/min; and (c) respiratory rate ≥ 30 times/min.
	- Endotracheal intubation again after surgery, ventilator-dependent time (non-invasive or invasive mechanical ventilation) ≤ 48 h.
**Grade 4**	- Respiratory failure: the postoperative ventilator-dependent time exceeds 48 h or the ventilator-dependent time exceeds 48 h after re-intubation.
**Grade 5**	- Death caused by respiratory system failure.

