The secondary outcomes of this study are as follows:Severity of pulmonary complications within 1 week: The severity of pulmonary complications will be assessed daily, until 1 week after surgery, using the worst score within a week for analysis. The modified PPC scoring table will be scored on an ordinal scale ranging from 0 to 5, in which grade 0 represents no pulmonary complications, grades 1–4 represent gradually deteriorating pulmonary complications, and grade 5 represents death of patients caused by respiratory diseases before discharge (Table 2).LUS: Lung ultrasound examination will be performed using the 2−5-MHz convex array ultrasonic probe of Edge (Sonosite Corporation, USA) before anesthesia (T0), 10 min after extubation (T1), 24 h after extubation (T2), and 72 h after extubation (T3). Twelve lung regions will be examined [26]; the lung on each side is divided into two areas by the fourth intercostal space: the upper and lower lung areas, and the upper and lower lung areas of the right and left lungs are delineated by the parasternal, anterior axillary, posterior axillary, and paravertebral lines. Therefore, both lungs are divided into 12 areas according to body surface markers. According to the improved scoring table (Table 3), the highest LUS of each lung area is 3 points and the lowest LUS is 0 points. Therefore, the total score of LUS ranges from 0 to 36 points. The higher the LUS, the more severe the atelectasis in this area [27].Regional cerebral oxygen saturation (rScO_2_): The 5100C brain and regional blood oxygen detection system (Covidien Corporation, USA) will be used to monitor rScO_2_ at T0, T1, T2, and T3. The mean value of the bilateral rScO_2_ will be considered as the rScO_2_. To ensure the accuracy of data, rScO_2_ will be collected 3 times, with an interval of 10 s each time, and the average value of the 3 values will be calculated.Arterial oxygen partial pressure/inspired oxygen fraction (PaO_2_/FiO_2_): arterial blood will be collected at T0, T1, T2, and T3 for blood gas analysis to determine the PaO_2_/FiO_2_.Postoperative ICU and hospital stays.Other research indicators include the duration of surgery and anesthesia, level and duration of PEEP, blood loss volume, blood transfusion volume, fluid input and urine output during surgery, and dosage of anesthetics and ephedrine during surgery (Table 4).

**Table 3 Tab3:** Scoring criteria for lung ultrasound images

Score	Ultrasonic image

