#### Sample size estimation and interim analysis

The main outcome of this study is the incidence of pulmonary complications 1 week after surgery. In the pre-test (20 cases in each group), the incidence of pulmonary complications 1 week after surgery in the P6 and Pi groups was 24% and 13.5%, respectively. Using the PASS15.0 procedure with *α* = 0.05 and *β* = 0.2, the minimum sample size of each group was calculated to be 216 cases. Based on the shedding rate of 20%, the number of cases included in each group will be at least 216 ÷ (1–20%) = 270. A total of 540 patients will need to be enrolled in the two groups in this study. The first patient was enrolled on 1 September 2021. The expected duration of the study is 25 months.

There will be a formal interim analysis performed by the Data Monitoring Committee to evaluate the efficacy of the primary outcome once 50% of the planned patients have been randomized and initiated intervention and have been followed up until discharge. The *p* value for the analysis will be set at *p*<0.001 using the alpha-sparing technique (O'Brien-Fleming) for benefit or harm. Stoping rules for adverse events: we will consider patients withdrawal from the trial if the following conditions occur. (1) severe brain swelling during surgery; (2) persistent hypotension and circulatory instability. 

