## Discussion

This study is a single-center randomized controlled trial to determine if the pulmonary impedance-guided individualized PEEP during the period from dura suturing to extubation reduces the incidence and severity score of pulmonary complications within 1 week following a craniotomy compared with a single PEEP. Considering the effects of anesthesia duration, age, insulin-dependent diabetes mellitus, and chronic obstructive pulmonary disease on PPCs [28], all patients will have a BMI ranging from 18.5 to 28 kg/m^2^, are 18~65 years of age without diabetes, and have co-existing lung diseases to avoid the effect of these factors on outcome. PPCs are defined as clinically relevant and identifiable lung changes that adversely affect the prognosis of patients. Because this definition lacks accuracy in the diagnosis of PPCs, the reported incidence of PPCs varies considerably [29]. Some researchers regard the comprehensive results of multiple lung diseases as lung complications, and others regard a specific lung disease or respiratory condition requiring special treatment postoperatively as lung complications [30, 31]. In this study, the improved PPCs score table will be used as the standard to evaluate the incidence of PPCs after surgery. The PPCs will be evaluated from multiple perspectives, such as symptoms, signs, blood gas analysis, and imaging changes, so that the evaluation is more systematic and comprehensive, and the severity of pulmonary complications can also be graded.

PEEP has been used clinically for more than 30 years because PEEP can prevent alveolar collapse, improve functional residual capacity, and improve lung dispersion and compliance [32–34]. Sreejit et al. [35] reported that the application of PEEP during mechanical ventilation under general anesthesia can effectively prevent alveolar collapse and expand the collapsed alveoli, thus improving hypoxemia; however, due to individual differences between patients, standardized and fixed PEEP cannot be applied to all patients. There is still controversy regarding the optimal level of PEEP during surgery [36, 37]. Franchineau et al. [38] conducted a study on individualized PEEP on 15 patients requiring extracorporeal membrane oxygenation, and the results showed that PEEP varies greatly among different patients, which suggested the necessity of individualized PEEP.

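### The only test stated for the primary outcome is unadjusted; a prespecified covariate-adjusted analysis would cost almost nothing and could gain a little power

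*Protocol article*

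**What the plan says.** Primary and secondary outcomes defines a yes/no endpoint: "The primary outcome of this study is the incidence of pulmonary complications within 1 week following surgery", counted when any item of Table 2 is present or the score is at least 1. Statistics assigns tests by data type only; count data will "be analyzed using the chi-square" or the Fisher exact test. No covariate-adjusted analysis of the primary outcome is named anywhere in the article.

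Baseline data are nevertheless planned. Table 1 (under Recruitment) lists sex, age, height, weight, BMI, ASA class and "Smoking (cases): never/ever/within 1 month before surgery". Primary and secondary outcomes schedules LUS "before anesthesia (T0), 10 min after extubation (T1") and at two later times, with PaO2/FiO2 at the same four times. The Discussion treats some patient factors as prognostic: "Considering the effects of anesthesia duration, age, insulin-dependent diabetes mellitus, and chronic obstructive pulmonary disease on PPCs". It then says that the restricted population is meant to keep these factors from affecting the outcome.

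Randomization describes 1:1 allocation and names no stratification factor: "Randomization will be achieved using a computer-generated randomization table".

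**The concern.** When baseline variables predict a binary outcome, a prespecified adjusted analysis of the same patients estimates the treatment effect more precisely than a comparison of raw proportions. Here the variables will be collected anyway, the protocol itself regards age as relevant, and T0 LUS grades atelectasis, which is one component of the primary endpoint. The design allows 20% for losses and is sized for 80% power on the patients who remain, so it has no reserve beyond that allowance. At stake are a modest amount of power and some protection of the estimate against chance imbalance in known predictors. The validity of the trial is not at stake.

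**Working it through.** **1. Inputs.** From Sample size estimation and interim analysis: 24% (P6) and 13.5% (Pi), "Using the PASS15.0 procedure with *α* = 0.05 and *β* = 0.2", 216 per group before losses, 20% loss. Sidedness is not stated; two-sided reproduces the figure. The strength of the covariates is given nowhere, so it is varied below as an assumption.

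**2. The plan's own figure.** Unadjusted two-sided comparison of two proportions with pooled variance under the null:

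n = [1.960 × √(2p̄q̄) + 0.842 × √(p₁q₁ + p₂q₂)]² / (p₁ − p₂)²

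- p̄ = (0.24 + 0.135)/2 = 0.1875, so √(2 × 0.1875 × 0.8125) = 0.552
- √(0.24 × 0.76 + 0.135 × 0.865) = √0.2992 = 0.547
- n = (1.082 + 0.460)² / 0.105² ≈ 215.7, rounded up to **216**; 216/0.8 = 270 per group, 540 in total

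The power of this test at 216 per group is 80.0%. Test, sample size and power target therefore agree.

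**3. Adjustment by approximation.** If baseline covariates explain a share R² of the outcome variance, the effective size is n/(1 − R²). At R² = 0.10, for example, 216/0.90 = 240.

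| Assumed R² | Power at 216 per group | n per group for 80% |
|---|---|---|
| 0 | 80.0% | 216 |
| 0.01 | 80.4% | 214 |
| 0.02 | 80.8% | 212 |
| 0.05 | 82.0% | 206 |
| 0.10 | 84.0% | 195 |
| 0.15 | 86.0% | 184 |

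**4. Adjustment by simulation.** 216 per arm, marginal rates held at 24% and 13.5%, one prognostic standard-normal covariate plus four useless ones in the model, 4,000 trials per setting. The adjusted test is that of the standardised risk difference.

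| Log-odds slope per SD (odds ratio) | Chi-square | Adjusted | Difference |
|---|---|---|---|
| 0 (1.00) | 80.6% | 80.8% | +0.2 |
| 0.25 (1.28) | 79.7% | 80.2% | +0.5 |
| 0.55 (1.73) | 79.9% | 81.9% | +2.0 |
| 0.80 (2.23) | 80.3% | 83.8% | +3.5 |

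The simulation error of each power figure is √(0.8 × 0.2/4,000) ≈ 0.6 points, so the first two rows show no clear difference. In a separate run with a single covariate and the Wald test of the log odds ratio (6,000 trials), chi-square against adjusted power was 80.8% v 80.1% at odds ratio 1.00, 81.2% v 81.1% at 1.28, 79.3% v 80.2% at 1.65 and 80.5% v 83.4% at 2.12. The pattern is the same, but the Wald test loses a little when the covariate is useless. That is a reason to let the standardised risk difference decide.

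**5. Chance imbalance.** With 216 per arm, the difference in means of a standardised covariate has standard error √(2/216) = 0.096. An imbalance above 0.15 SD in either direction (0.15/0.096 = 1.56 standard errors) therefore arises in about 12% of trials. In simulation, an imbalance of 0.1 SD moved the unadjusted risk difference by about 0.8 points (slope 0.55) to 1.1 points (slope 0.80), against a planned effect of 24 − 13.5 = 10.5 points. The adjusted estimate moved by less than 0.05 points.

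**6. Can the data carry the model?** Expected events at the final analysis are 216 × 0.24 + 216 × 0.135 = 81. Arm, age, smoking (two coefficients), BMI and T0 LUS make six coefficients, so 81/6 = 13.5 events each. At the interim (135 per arm, or 108 after 20% loss) about 51 or 41 events are expected, that is about 8 or 7 each. The list should be kept short.

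**The case against.** The case against acting is substantial, and much of it stands.

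- The chi-square is a valid test for a 1:1 randomised binary endpoint and matches the sample size calculation. This stands: nothing is stated wrongly or contradicted.
- Adjusted models are often left to a statistical analysis plan, which is not shown. This stands as a caution. The point is confined to the test that the article does state, and it lapses if the plan already adjusts.
- The Discussion handles prognostic factors by restriction: ages 18-65, ASA I-II, BMI 18.5-28, chronic lung disease excluded. Of the four factors it names, only age is usable as a covariate, since anesthesia duration is completed after randomisation and diabetes and COPD are meant to be absent. It nowhere calls smoking or T0 LUS prognostic. This stands as a limit on the likely gain, although 18-65 still spans 47 years.

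Two stronger readings are tempting. A reader might infer that a known amount of power is being wasted, for instance that adjustment would bring the trial to 84-86%. Those figures require a log-odds slope of about 0.8 to 1.1 per SD (odds ratios 2.2 to 3.0), and nothing in the article supports predictors that strong in so homogeneous a population. A reader might also infer that unstratified allocation leaves the unadjusted result biased. It does not: the chi-square's error rate already allows for chance imbalance, and with no stratification factor described, none is being ignored.

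**Conclusion.** The point holds as an optional but worthwhile efficiency improvement. Under the planned rates and 216 evaluable patients per group, 0 to 2 points is the more plausible gain given the eligibility limits; the 3 to 4 points seen at a slope of 0.8 would need strong predictors. These figures rest on assumed covariate strength and on simulated normal covariates, not on anything the article reports. The second benefit, an estimate less disturbed by chance imbalance, applies only to covariates in the model, and its size depends on the same assumed slopes. Because the data are already planned and the risk of loss is negligible, the change is worth making, but the trial remains sound without it.

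**What to change.** Before any interim outcome data are seen, write into the analysis plan:

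- Primary analysis: logistic regression of pulmonary complication within 7 days (yes/no) on arm, age, smoking (three levels), BMI and T0 LUS.
- Deciding result: the standardised (marginal) risk difference with its 95% CI and p-value. The same analysis is used at the interim and at the final look, so that only one p-value decides at each.
- Supportive analysis: the chi-square or Fisher test as now stated.
- Anesthesia duration is not a covariate, because it is completed after randomisation.

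The cost is a paragraph of wording and a short script, since the standardised risk difference may lie beyond the SPSS menus. No new data and no further patients are needed, and the sample size of 216 per group (270 with losses) can stay as it is.

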**Methods:**

A randomized controlled trial will be conducted at the Second Affiliated Hospital of Soochou University. Five hundred forty patients undergoing a craniotomy in the supine position will be randomly allocated into the P6 (PEEP = 6 cmH_2_O) or Pi (individualized PEEP) group. Both groups of patients will receive a lung recruitment maneuver before suturing the dura. Then, the P6 group will receive 6 cmH_2_O PEEP, and the Pi group will receive EIT-guided individualized PEEP. The incidence and severity score of pulmonary complications within 1 week following surgery, the lung ultrasound score (LUS), regional cerebral oxygen saturation (rScO_2_), and PaO_2_/FiO_2_ before anesthesia (T0), 10 min after extubation (T1), 24 h after extubation (T2), and 72 h after extubation (T3) will be compared between the two groups. The duration of surgery and anesthesia, the level and duration of PEEP during surgery, the volume of liquid intake and output during surgery, and the postoperative ICU and hospital stays will be recorded. The main outcome of this study will be the incidence of pulmonary complications within 1 week after surgery.

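### Between-group tests of LUS, rScO2 and PaO2/FiO2 leave out the T0 value and so lose precision; the within-group ANOVA does not compare treatments, and the mixed model is named only for missing values

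*Protocol article*

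**What the plan says.** The Primary and secondary outcomes section lists three continuous secondary outcomes with the same four time points: before anaesthesia (T0), then 10 minutes, 24 hours and 72 hours after extubation (T1, T2, T3). Lung ultrasound is scored at these times, the cerebral oximeter is used "to monitor rScO_2_ at T0, T1, T2, and T3", and for PaO2/FiO2 "arterial blood will be collected at T0, T1, T2, and T3 for blood gas analysis". The Methods part of the Abstract states the question: these measurements "will be compared between the two groups".

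The Statistics section then names the tests:

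- Normally distributed variables: "Two independent sample *t*-tests will be used for comparison between groups".
- Time course: "analysis of variance (ANOVA) will be used for comparison at different time points within the groups".
- Skewed variables: "the Mann-Whitney *U* test will be used for comparison".

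The section mentions no baseline covariate, change from baseline or group-by-time term. Its last sentence assigns missing values to a mixed model for repeated measurements. It does not say whether that model supplies the treatment comparison, or whether T0 enters it.

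**The concern.** T0 precedes the intervention, because both groups are ventilated in the same way until dura suturing begins. It is therefore a legitimate baseline covariate, and it is already being collected, including an arterial sample. None of the named between-group tests uses it. If T0 predicts the later values, those tests carry between-patient variation that could be removed at no cost.

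The one analysis that links the time points is run inside each group. It shows whether values move over time in that group, not whether the groups differ.

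The mixed model has an unclear role. A model of this kind estimates the group difference directly from all observed values. It does not fill in data for a t-test or an ANOVA. As written, two different analyses could each be taken as the planned one for the same outcome.

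The Discussion uses PaO2/FiO2 and regional brain oxygen saturation to judge the effectiveness and safety of individualised PEEP, so the precision of these comparisons matters.

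**Working it through.** **The plan's own figure.** The only stated sample size is for the binary primary outcome: 24% against 13.5%, alpha 0.05, power 80%. The two-sided pooled formula without continuity correction is

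n = [1.960 × √(2 × 0.1875 × 0.8125) + 0.842 × √(0.24 × 0.76 + 0.135 × 0.865)]² / (0.105)²

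This gives 215.7, so 216 per group. Then 216 / 0.8 = 270 per group and 540 in total. The stated figures reproduce, and this point does not touch them. The article gives no standard deviation, effect size or correlation for LUS, rScO2 or PaO2/FiO2.

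**Precision lost by leaving out T0.**

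Inputs: 216 per group after dropout (Sample size estimation and interim analysis section); two-sided 5% level, the two-sidedness being assumed; correlation r between T0 and one follow-up value, assumed to be 0.1 to 0.7.

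- Unadjusted t-test at one time: the difference detectable with 80% power is (1.960 + 0.842) × √(2/216) = 0.270 SD.
- With T0 as covariate, the residual variance is SD² × (1 − r²). The detectable difference becomes 0.270 × √(1 − r²), and the number per group for equal power becomes 216 × (1 − r²).
- Power for the same 0.270 SD becomes Φ(2.802/√(1 − r²) − 1.960). At r = 0.1 this is Φ(2.816 − 1.960) = Φ(0.856) = 80.4%.

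| Assumed r | Variance cut | Detectable difference (SD) | Power for 0.270 SD | n per group for equal power |
|---|---|---|---|---|
| 0.1 | 1% | 0.268 | 80.4% | 214 |
| 0.3 | 9% | 0.257 | 83.6% | 197 |
| 0.5 | 25% | 0.233 | 89.9% | 162 |
| 0.7 | 49% | 0.193 | 97.5% | 110 |

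The table applies to a linear model at one time point. It does not carry over to an outcome sent to the Mann-Whitney test.

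**Why within-group results cannot stand in for a comparison.** Suppose both groups have the same true change over time, and each within-group test has 80% power. The chance that exactly one of them is significant is 2 × 0.8 × 0.2 = 32%, although the groups do not differ.

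**If the ANOVA were an ordinary one-way analysis.** The text does not say which type is meant. One group of 216 patients with four equally correlated values and no true change over time was simulated 4,000 times. At a nominal 5%, the one-way ANOVA rejected in about 1.3% (r = 0.3), 0.2% (r = 0.5) and 0% (r = 0.7) of runs. Ignoring the pairing would make the time test conservative. It would not produce excess false positives.

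**The case against.** Five points can fairly be made for the plan.

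1. **The between-group tests are sound.** With 1:1 randomisation, an unadjusted comparison at T1, T2 or T3 is unbiased. This stands. A reader might infer that the plan answers the wrong question for these outcomes. It does not: the t-test and the Mann-Whitney test address the stated between-group aim, and only the within-group ANOVA does not.

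2. **T0 is not ignored altogether.** It is one of the time points in the ANOVA. This stands; what is missing is T0 as a covariate in the treatment comparison.

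3. **ANOVA may mean repeated-measures ANOVA.** The same paragraph names a repeated-measurements model, and a condensed article may omit the type. This stands. A reader might infer that the plan treats repeated values from one patient as independent, but the text does not say so. If it did, the error would be on the conservative side.

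4. **No false claim is planned.** Nothing in the article says that significance in one group alone will be taken as a treatment effect. This also stands; the 32% shows why such a reading should be ruled out, not that the plan makes it.

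5. **The gain is assumed and may be small.** Patients are ASA I–II, and chronic lung disease, pneumonia and atelectasis are among the exclusions. LUS at T0, on a scale of 0 to 36, may therefore lie near zero and predict little. This stands for LUS in particular.

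One further argument does not succeed: that all of this belongs to an analysis plan or full protocol not shown. The article does name the tests for these outcomes, and names them without T0. The mixed-model sentence does not repair this, because it is confined to missing values and is silent on T0.

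**Conclusion.** The point holds as a matter of precision and clarity, not of validity. For three secondary outcomes the plan fixes between-group tests that leave out an available baseline, adds a within-group test that does not compare treatments, and gives the mixed model a role that it cannot fill alongside t-tests.

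The size depends entirely on an assumed correlation: a variance cut of 1% at r = 0.1, rising to 49% at r = 0.7. A reader might take the upper end as the expected gain, since it is equivalent to 1/(1 − 0.49) = 1.96 times as many patients. The documents do not support choosing that end, and for LUS the lower end is plausible. The figures also assume a roughly linear relation between T0 and follow-up, and one follow-up time at 216 per group.

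This is an improvement worth making because it costs nothing in data.

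**What to change.** In the Statistics section, for each of LUS, rScO2 and PaO2/FiO2:

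- Make the mixed model for repeated measurements, which the plan already names, the between-group analysis. Use T1, T2 and T3 as responses, with group, time, group × time, and the T0 value as covariate.
- Report the adjusted between-group difference with its 95% confidence interval at each of T1, T2 and T3.
- Present within-group changes over time descriptively, and do not base inference about treatment on them.
- Keep a rank-based or transformed sensitivity analysis for skewed outcomes such as LUS, so that the plan's provision for skewness is not lost.
- Reword the missing-values sentence to say that this model uses all observed values and is itself the analysis.

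The cost is a change of wording, made before group-level results are seen. No new measurements, patients or visits are needed, and the primary analysis and the total of 540 stay as they are.

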^*^Only when two or more conditions occur at the same time, it is classified as grade 2

Bedside chest radiographs will be obtained for all patients at the first, third, fifth, and seventh postoperative days, in addition to those requested by the staff surgeons. They are independently analyzed by 2 pulmonary specialists, blinded to the grouping. Only concordant assessments (an abnormal opacity at the same location) will be integrated into clinical findings for the final score of pulmonary complications. The occurrence of pulmonary complications will be assessed daily, until the 7th day following surgery.

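### The stated missing-data rule, a mixed model for repeated measurements, cannot handle a missing yes/no primary outcome, and the sections do not agree on the denominator

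*Protocol article*

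**What the plan says.** All places are in the protocol article.

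- **Outcome** (Primary and secondary outcomes): "The primary outcome of this study is the incidence of pulmonary complications within 1 week following surgery". A patient counts as a case with any listed sign or a score of at least 1. On timing: "The occurrence of pulmonary complications will be assessed daily, until the 7th day following surgery".
- **Formula** (same section): incidence is "number of cases with pulmonary complications/total number of patients in this group".
- **Test** (Statistics): count data will "be analyzed using the chi-square (*χ*^2^) test or Fisher exact test".
- **Missing data** (Statistics): "Missing values will be handled by the mixed model for repeated measurements". The sentence names no outcome and makes no exception.
- **Analysis set** (Statistics): "Intention-to-treat will be considered for the patients with an incomplete follow-up period".
- **Planned loss** (Sample size estimation and interim analysis): "Based on the shedding rate of 20%, the number of cases included in each group will be at least 216", which is then divided by 0.8 to give 270 per group. The planning incidences "in the P6 and Pi groups was 24% and 13.5%, respectively".

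**The concern.** A mixed model for repeated measurements, in its usual sense, is fitted to a continuous variable measured several times per patient. It suits the lung ultrasound score, rScO2 and PaO2/FiO2, each taken at T0 to T3. The primary outcome is a single binary value that enters a 2×2 table. The model produces no entry for that table, so the only rule given does not work for the endpoint that decides the trial.

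Three statements then bear on who is counted, and they do not fit together. The formula divides by all patients in the group. Intention-to-treat is to be considered when follow-up is incomplete. The sample size treats the lost fifth as contributing no information.

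Two things are at stake. The analysis set could be chosen after the data are seen. And if unknown status is entered as no complication, both incidences are pulled down, and unequal loss between arms biases the comparison. Unequal loss is possible: the interim-analysis section lists marked brain swelling and sustained low blood pressure as grounds for considering withdrawal, and the Introduction and Discussion say that PEEP may affect intracranial pressure and circulation.

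**Working it through.** **Inputs from the article:** 24% (P6) and 13.5% (Pi); α = 0.05; power 80%; 216 evaluable and 270 enrolled per group; 20% loss; 1:1 allocation. Sidedness is not stated; two-sided reproduces the plan's figure.

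**Inputs that are assumptions:** the unequal loss splits; the share of dropouts' events recorded before they leave; and that dropouts have the same true incidence as others in their arm.

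**Step 1. Reproduce the plan.** Pooled-variance formula without continuity correction, with mean incidence (0.24 + 0.135)/2 = 0.1875:

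n = [1.960 × √(2 × 0.1875 × 0.8125) + 0.842 × √(0.24 × 0.76 + 0.135 × 0.865)]² / 0.105² = 215.7, rounded up to 216.

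216/0.8 = 270. Both figures match. Power is 80.0% with 216 observed per arm, and would be 88.0% if all 270 were observed.

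**Step 2. Compare the denominators.** Planned loss is 270 − 216 = 54 per arm. Expected events among 216 observed are 216 × 0.24 = 51.8 and 216 × 0.135 = 29.2, a gap of about 23. The patients with potentially unknown status outnumber the gap in events, so their handling matters.

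**Step 3. The literal reading.** Keep 270 in the denominator and enter a dropout with no recorded complication as a non-case. With loss d and share c of dropouts' events recorded before leaving, the apparent incidence is q = p × [1 − d × (1 − c)].

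The rejection probability uses the two-sided pooled z-test at n = 270: Φ((−1.960 × s0 − D)/s1) + 1 − Φ((1.960 × s0 − D)/s1). Here D = q1 − q2, s0 = √(2 × q̄ × (1 − q̄)/n), q̄ is the mean of q1 and q2, and s1 = √([q1(1 − q1) + q2(1 − q2)]/n).

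*Equal 20% loss, effect as planned*

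| c | P6 | Pi | Difference | Power |
|---|---|---|---|---|
| 0 (extreme) | 0.24 × 0.8 = 19.2% | 0.135 × 0.8 = 10.8% | 8.4 points (10.5 planned) | 78.2% |
| 0.5 | 0.24 × 0.9 = 21.6% | 0.135 × 0.9 = 12.15% | 9.45 points | 83.6% |

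With equal loss and no true effect, the type I error stays at 5.0%.

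*No true effect (24% in both arms), assumed unequal loss P6 vs Pi*

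| Loss | c | Apparent incidences | Type I error |
|---|---|---|---|
| 15% vs 25% | 0 (extreme) | 20.4% vs 18.0% | 10.9% |
| 15% vs 25% | 0.5 | 22.2% vs 21.0% | 6.3% |
| 10% vs 30% | 0 (extreme) | 21.6% vs 16.8% | 29.3% |
| 10% vs 30% | 0.5 | 22.8% vs 20.4% | 10.4% |

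At c = 0.75 the two type I errors are 5.3% and 6.3%.

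*Effect as planned, assumed unequal loss, c = 0.* With 25% loss in P6 and 15% in Pi, power is 57.1%. With 15% and 25%, it is 91.5%. The bias can run either way.

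**The case against.** The strongest reply is that the denominator problem is inferred. The formula is an ordinary definition of an incidence, placed beside the scoring table, and not a missing-data rule. The group total could mean those analysed, and inflating 216 to 270 is routine and supports that reading. **This stands.** A reader might infer that the plan counts every dropout as complication-free, but the article does not say so. Even on the literal reading it would not follow, because complications are assessed daily and a patient with one recorded before leaving is already a case.

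A second reply is that the error rates are extreme. **This also stands.** The figures with c = 0 assume that no dropout has a recorded event, and the 15/25 and 10/30 splits have no source in the article. No withdrawal rates by arm are given. Both arms undergo the same recruitment steps, and the pre-test median individualised PEEP equals the control level, so a large imbalance is possible but not shown. The 20% is a planning allowance, not a forecast of missing day-7 assessments.

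A third reply is that imputation details belong in an analysis plan that is not shown. That holds for the choice of method and variables, whose absence is no fault here. **It does not rescue the stated rule.** The article fixes a rule for all missing values, and it does not work for the primary outcome. A binary or ordinal mixed model on the daily scores is conceivable, but the article does not plan one.

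**Conclusion.** The point holds in two parts. First, the one stated missing-data rule cannot handle a missing primary outcome. This follows from the text alone and needs no assumption. Second, the incidence formula, the intention-to-treat sentence and the sample size do not agree on the denominator, so the primary analysis set is open. The article does not fix dropouts as non-cases; that is only the literal reading of two sentences taken together.

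The size depends on the loss. Equal loss matters little: 78.2% power in the extreme case, 83.6% if half of the dropouts' events are recorded, and no inflation of type I error. The real risk is loss that differs by arm or is related to outcome. Under the assumed splits, type I error runs from 6.3% to 10.9% (15% vs 25%) and from 10.4% to 29.3% (10% vs 30%), depending on whether half or none of the dropouts' events are recorded. These figures show sensitivity and do not predict what will happen in this trial. The sample size itself is arithmetically sound.

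**What to change.** 1. Confine the mixed model for repeated measurements to the lung ultrasound score, rScO2 and PaO2/FiO2.
2. Define the primary analysis set as all randomised patients by assigned arm, and align the incidence formula and the sample-size text with it.
3. Count any complication recorded by day 7 as an event, whether or not follow-up was completed.
4. For patients with no recorded event and incomplete days 1 to 7, name a method suited to a binary outcome. Multiple imputation by arm, using the daily scores, baseline variables and available T1 to T3 data, is one option; other valid methods would also do.
5. Add a best/worst-case or tipping-point sensitivity analysis.

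Settle this before any comparison by arm, including the efficacy look planned at 50% of patients. The cost is a few lines of text and some programming, with no new data.
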